## Abstract

**Background:**

Successful cancer treatment can lead to cancer survivors being predisposed to an increased lifelong risk of adverse late health effects. Therefore, high-quality cancer survivorship care to earlier detect and treat late effects or to preserve survivor’s health is essential. Nevertheless, this care needs to be sustainable and cost-effective as well. We developed three different screen-to-screen nurse-led eHealth interventions for survivors of childhood, adolescent and young adult-onset cancer, collectively called the REVIVER interventions. Elaborating on person-centred care principles with content based on cognitive behavioural therapy modules and/or motivational interviewing techniques, these interventions aim to empower and coach survivors to improve (1) symptoms of cancer-related fatigue, (2) self-efficacy and self-management or (3) lifestyle. With the REVIVER study, we aim to evaluate the interventions’ feasibility and gain insights into the potential effectiveness.

**Methods:**

The REVIVER study involves a mixed methods design, including (1) interviews till data saturation with cancer survivors who completed the interventions as well as with all involved medical professionals, (2) reviews of nurses reports and (3) a single-group, pre-post evaluation among cancer survivors. Eligible survivors are survivors of childhood, adolescent and young adult-onset cancer who are referred to one of the interventions, in complete remission of cancer, 16–44 years old at enrolment, completed treatment at least 5 years ago and have access to a device with Internet options. We will assess feasibility in terms of demand, adherence, acceptability, practicality and integration/implementation. Health-related quality of life, as primary outcome of the potential effectiveness evaluation, will be assessed at three different time points: prior to the intervention; immediately following the intervention and 6 months post-intervention. Secondary outcome measures include changes in level of fatigue, self-efficacy, self-management and lifestyle.

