### REVIVER interventions

In order to treat survivors for late effects of cancer treatment in a cost-effective way with limited burden, an eHealth solution for survivors of childhood, adolescent and young adult (CAYA) cancer was developed and has recently been implemented at the Centre of Expertise for Cancer Survivorship. These so-called REVIVER interventions, with PCC as core principle, are part of cancer survivorship care to improve the following direct or indirect late effects of cancer treatment: CRF, self-efficacy and self-management or lifestyle. The interventions are led by a trained nurse who applies either cognitive behaviour therapy (CBT), motivational interviewing (MI) or a combination of both to help survivors overcome their late effects. However, there is a need for feasibility and potential effectiveness evaluations in order to implement the REVIVER interventions on a wider scale.

Our primary study objective relates to the assessment of the feasibility of the REVIVER interventions and can be broken down into two specific objectives:
Determine feasibility of the REVIVER interventions for CAYA cancer survivors, in terms of:
DemandAdherence to the sessionsAcceptability (e.g. content and delivery)Practicality (e.g. mode of delivery)Integration/implementation (e.g. facilitators and barriers)
2.Determine feasibility of the REVIVER interventions for the medical professionals, in terms of:
Acceptability (e.g. content, delivery and referral to interventions)Practicality (e.g. mode of delivery)Integration/implementation (e.g. facilitators and barriers)

Our secondary objective is to gain insight into the potential effectiveness of the REVIVER interventions in CAYA cancer survivors, in terms of quality of life, fatigue, self-efficacy, self-management and lifestyle.

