### Design

The REVIVER study will involve a mixed methods research approach. Feasibility will primarily be assessed with qualitative measures, i.e. semi-structured interviews. Quantitative measures will be used to determine adherence to and gain insight into the potential effectiveness of the REVIVER interventions. Therefore, we will apply a single arm pre- and post-test design, with three different measurement points: baseline (T0), following the last session (T1) and 6 months post-intervention (T2). Figure 1 outlines the stages of participation in the REVIVER study interventions.

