### REVIVER interventions

The REVIVER interventions are designed for CAYA survivors to receive coaching to cope with direct or indirect late effects of cancer and are delivered by qualified nurses via secured screen-to-screen video calling software. The interventions, elaborating on PCC principles, are aimed at improvement of (i) symptoms of CRF, (ii) self-efficacy and self-management or (iii) lifestyle. The REVIVER interventions consist of an intake, 3 to 6 screen-to-screen video-coaching sessions and a reflection session. On average, the intake session as well as the coaching sessions will be delivered within a 3-month time period. After a 6-month period in which the survivor can actively work on his or her goals set during the coaching sessions, a reflection session will follow. Depending on the type of intervention, the content is based on CBT and/or MI techniques (Table 2). Fidelity of the REVIVER interventions will be pursued in the three following ways:

**Table 2 Tab2:** REVIVER interventions

Goal	To empower, to motivate and to coach CAYA survivors to actively work on improving and managing either CRF, self-efficacy and self-management or lifestyle
Type	Individual eHealth nurse-led video-coaching interventions delivered during screen-to-screen sessions
Duration	An intake session, 3–6 coaching sessions over a time course of approximately 3 months, and a 6-month follow-up reflection session. Average duration of each session is 30–45 min
Basic principle	Person-centred care
Structure	
• Phase 1 (intake) *Engaging with survivor/focus setting*	During the intake, the nurse will reflectively listen to the survivor’s narrative, try to build a mutually trust with the survivor and explore the survivor’s stage of change. Focus for the following sessions will be discussed
• Phase 2 (3–6 sessions) *Coaching with evidence-based modules of CBT and/or MI*	According to needs and preferences of the survivor, 3–6 coaching sessions will follow Content of the interventions: o *CRF*: module of cognitive behaviour therapy light for chronic fatigue after cancer [31] o *Empowerment*: module cognitive behaviour therapy on four-phase recovery for cancer survivors and motivational interviewing for goal setting [32] o *Lifestyle*: motivational interviewing according to the stage of change of survivor [33]

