#### 3. Adherence of nurses to intervention protocol according to survivors

Following the last coaching sessions, a number of survivors are asked to participate in an interview on facilitators and barriers of the interventions. In this interview, survivors are also asked on the important components of the intervention protocol to check adherence of the nurses to the protocol.

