#### Feasibility evaluation

The survivors for feasibility evaluation will be recruited from the sample of survivors of the potential effectiveness evaluation part of the REVIVER study. During the last video calling session of the REVIVER intervention, the nurse will approach survivors to ask consent to participate in an interview and to be audio recorded. The interviews will take place in the weeks following the last session of the intervention. Beforehand, the researcher will explain the goals for doing this research. Average duration of each interview will be approximately 45–60 min.

Likewise, at the end of the study period, interviews with an average duration of 30–45 min will be conducted with the medical professionals by the same researcher with the medical professional’s consent for audio to be recorded.

An interview guide for the survivors will be developed by the researchers to (semi)structure the interviews (available on request). The guide will contain questions on mode of delivery, content and delivery and facilitators and barriers of the interventions. It will conclude with the survivors’ intentions to continue using the learned strategies to cope with symptoms of fatigue and low self-efficacy level or to adopt/maintain a healthy lifestyle in daily life. For medical professionals, the focus of the guide will be on the practicality of the interventions, fit within the organizational culture and perceived facilitators and barriers. The interview guide will be tested as a pilot in CAYA cancer survivors and other medical professionals affiliated with the Centre of Expertise for Cancer Survivorship. The survivors and medical professionals will be interviewed by an independent researcher who is not involved with the interventions. Both the survivors and medical professionals will be provided with a summary of the results following the end of the study. The nurses’ reports, written after each session with the survivor, will be analysed to assess adherence to the interventions.

These reports contain information on duration and frequency of the sessions, type of module/phase of MI, goals set and goals completed by the survivor. In addition, data on perceived facilitators and barriers of the REVIVER intervention will be collected from the reports as well.

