### Outcome measures

#### Feasibility evaluation

The outcome measures for both samples of participants will be mainly based on guidelines from Bowen et al. to assess the feasibility of the REVIVER interventions, including [42]:
*Demand*Outcomes of interest for demand of the interventions include whether the survivors prefer the REVIVER intervention to care as usual, whether the survivors intend to continue applying the content of the interventions in daily life and whether the medical professionals perceive demand for using the REVIVER interventions in daily practice.*Adherence of survivors with interventions (actual use)*Outcome of interest for adherence with the interventions includes the percentage of planned sessions joined by the survivors.*Acceptability*Outcomes of interest include the satisfaction and perceived appropriateness in both survivors and medical professionals with the content and delivery of the REVIVER interventions and fit within the organizational culture.*Practicality*Outcomes of interest include the experiences with the mode of delivery of the REVIVER interventions for both survivors and medical professionals in terms of efficiency, ability to carry out the intervention activities and positive and negative effects on the survivors*Integration/implementation of the REVIVER interventions*Outcomes of interest include success or failure of the REVIVER interventions and perceived facilitators and barriers of success or failure of the REVIVER interventions for both survivors and medical professionals.

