#### Potential effectiveness evaluation

All analyses will be conducted with the statistical software program SPSS (v25). Descriptive analyses will be conducted using mean with standard deviation, median with interquartile range and frequency for baseline characteristics. These variables include gender, age at intervention and treatment, socio-economic status, previous cancer diagnosis and treatment received. The validated questionnaires will be scored and analysed according to the instructions given by the authors of the questionnaires [49]. Potential covariates such as duration and amount of sessions per survivor will be presented as mean and standard deviation as well. To examine differences in the outcome measures over time, a mixed effect model with random intercept and slope will be used. In total, two nurses are assigned to deliver the interventions. The nurse who delivers the interventions may influence the survivor’s outcome. Therefore, nurse is here considered as a random effect. The outcome measures will serve as independent variables in this model with time and potential covariates as dependent variables. Tukey’s HSD test will be used as well to adjust for multiple comparisons. Due to limited power of our study, we will report data with 95% confidence intervals where needed. In addition, all data of our hypothesis testing will be treated as preliminary and with caution. Lastly, we will analyse all data according to the intention-to-treat analyses.

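### Survivor interviews, the main method for the primary feasibility objective, reach only people who finished the coaching; those who stop early have no route into the sample

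*Protocol article*

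**What the plan says.** The Background, under REVIVER interventions, sets the priority: "Our primary study objective relates to the assessment of the feasibility of the REVIVER interventions". Methods, Design, names the main tool: "Feasibility will primarily be assessed with qualitative measures, i.e. semi-structured interviews".

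Three places describe who is interviewed and how they are reached:

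- Abstract, Methods: "interviews till data saturation with cancer survivors who completed the interventions".
- Study procedures, Feasibility evaluation: "During the last video calling session of the REVIVER intervention, the nurse will approach survivors to ask consent to participate in an interview".
- The third fidelity item, on nurses' adherence as seen by survivors: "Following the last coaching sessions, a number of survivors are asked to participate in an interview on facilitators and barriers of the interventions". Table 3 likewise places the interview at T1.

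The sample size section adds that sampling is purposive, from survivors in the effectiveness part, with saturation expected at about 15; Table 3 gives 10–15. The analysis section states: "In total, two nurses are assigned to deliver the interventions".

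On adherence, the outcome section says that the measure "includes the percentage of planned sessions joined by the survivors". Table 2 sets the number of sessions: "According to needs and preferences of the survivor, 3–6 coaching sessions will follow". The data come from the reports that nurses write after each session.

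**The concern.** The feasibility outcomes include whether the interventions succeed or fail, what helps or hinders them, whether survivors can carry out the activities, and any negative effects. Survivors who gave up are the most direct source on all of these. A sample recruited at the final session does not contain them, and purposive selection cannot add people who never reach the point of invitation.

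The inviting nurse is also one of the two who deliver the coaching, and the same interviews are used to check how well the nurses kept to the intervention protocol. The people being assessed therefore approach those who will assess them.

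At stake is the decision that the abstract attaches to the result: a randomized trial follows if the interventions prove feasible and potentially effective. The Discussion also looks to this study for areas to improve. Its limitations name the lack of a control group and the small size, but not this selection.

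Adherence raises a lesser issue. If the planned number of sessions can be lowered during coaching, a survivor who loses interest and agrees with the nurse to stop looks the same as one who completed a full course.

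**Working it through.** **The plan's own figures.** About 48 survivors per month × 24 months × 1/10 = 115.2 (stated 116). At 50% recruitment, 0.50 × 116 = 58 (stated 60). Both reproduce within rounding. They set the scale only and neither support nor refute the point.

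**The sampling frame, passages side by side.** The abstract restricts interviewees to completers. Study procedures puts the invitation in the last video session. The fidelity item and Table 3 put the interview after the last coaching session. These agree with one another, and no section offers another route. A survivor who leaves before a closing session therefore has probability zero of being interviewed.

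**What an unrestricted draw would do.** The drop-out proportions are assumptions, because the article gives none. With 60 enrolled, d early stoppers and 15 drawn at random, P(no early stopper) = C(60 − d, 15) / C(60, 15):

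| Assumed early stopping | d | P(none among 15) | Expected among 15 | P(none), described frame |
|---|---|---|---|---|
| 10% | 6 | 0.16 | 1.5 | 1 |
| 20% | 12 | 0.02 | 3.0 | 1 |
| 30% | 18 | 0.002 | 4.5 | 1 |

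**How far the picture could shift.** Let s be the share who stop early, p_c the share of completers who find the intervention acceptable, and p_n the same share among early stoppers. Overstatement = p_c − [(1 − s)p_c + s·p_n] = s(p_c − p_n). All rates are assumed, with p_c = 0.90:

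- s = 0.20, p_n = 0.60: 0.20 × 0.30 = 6 points.
- s = 0.20, p_n = 0.30: 0.20 × 0.60 = 12 points.
- s = 0.40, p_n = 0.60 to 0.30: 12 to 24 points.
- p_n = 0.90: 0 points at any s.

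Qualitative interviews do not estimate a proportion, so this shows only the direction and what drives it.

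**Adherence.** Adherence = sessions joined / sessions planned, with 3 to 6 coaching sessions:

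- 3 joined: 3/3 = 100% if the plan is 3, and 3/6 = 50% if it is 6.
- 4 joined: 4/4 = 100% or 4/6 = 67%.
- 5 joined: 5/5 = 100% or 5/6 = 83%.
- 2 joined: at most 2/3 = 67%, so leaving below the minimum always shows.

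The ambiguity is therefore confined to survivors who attend at least three sessions and whose plan is shortened along the way. The article does not say when the planned number is set.

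**The case against.** The strongest reply is that early stoppers are not invisible. Nurses report after every session, so the reports include people who later leave, and barriers, goals set and goals completed are drawn from them. A checklist follows each session as well. All nine professionals are interviewed, and demand and acceptability are read partly from them. An independent researcher conducts the interviews, which limits politeness towards the nurse in what survivors say. All of this stands. It narrows the gap but does not close it: the reports and professional interviews give the professional's view of why a survivor stopped, and an independent interviewer does not change who was invited.

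A reader might go further and infer that adherence will be close to full whatever the drop-out. The text does not support that. Missed planned sessions lower the figure, as does leaving before the third coaching session. Three sessions chosen by need is a full course under Table 2, so scoring everyone against six would be wrong. The number of sessions is also summarised by mean and SD, so a drift towards three could be seen. The full protocol may fix the planned number at intake.

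A reader might also count the roughly 58 eligible survivors who do not enrol as lost evidence on barriers. They did not join the study, but consent is sought after referral and the interventions are usual care at this clinic, so they have not necessarily refused the coaching.

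**Conclusion.** The point holds for the survivor interviews. Followed as written, the plan leaves early stoppers out of the main method for its primary objective, and what replaces their accounts is second-hand. The likely lean is towards a favourable reading, on the assumption that people who stop are less satisfied or met more barriers than those who finish. The size cannot be stated: no drop-out rate is given, and the lean is zero if the two groups share the same views or if nobody stops. It would be too much to say that the feasibility conclusion as a whole is biased. The professional interviews are not drawn from completers, and the adherence percentage can cover all participants.

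The adherence point is secondary and conditional. It matters only if the planned number can be revised after intake, which the article leaves open.

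**What to change.** Change the Abstract (Methods) and Study procedures (Feasibility evaluation) so that the purposive sample is drawn from all enrolled survivors rather than completers. Reserve a few of the roughly 15 interviews, for example 3–5, for survivors who stopped early, if there are any. Let the independent researcher, not the treating nurse, make the invitation from the enrolment list.

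For adherence, state that the denominator is the number of sessions planned at intake, and report the number attended beside it. A completion measure set at three coaching sessions would not help, because it counts an agreed stop after three sessions as a success.

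No extra interviews or staff are needed; slots are reallocated and the existing nurse reports supply the session data. The cost is fewer completer interviews: 15 − 3 = 12 or 15 − 5 = 10, which is about 4 or 3.3 per intervention instead of 5, and saturation within an intervention may be harder to reach. Early stoppers are also harder to contact. If the recruitment route cannot be changed, the selection should be listed among the limitations in the Discussion.

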**Discussion:**

This is the first study to evaluate the feasibility and potential effectiveness of eHealth nurse-led interventions elaborating on person-centred care, using cognitive behavioural therapy and/or motivational interviewing techniques as an innovative and promising approach for providing CAYA cancer survivorship care. If the interventions prove to be feasible and potential effective, a randomized controlled trial will be conducted to test the (cost)-effectiveness.

## Background

In the last decades, worldwide survival rates for patients with cancer have improved. As a result, the number of cancer survivors is rapidly increasing [1–3]. However, a disadvantage of successful treatment is that, due to chemotherapy and/or radiotherapy, cancer survivors are predisposed to an elevated lifelong risk of late adverse health effects [4–7]. These late effects, which may appear even years or decades after treatment, can be serious, leading to chronic morbidity and premature mortality [5].

### Late effects of cancer treatment

Late effects of cancer treatment can have a negative impact on multiple dimensions of health, including physical and psychosocial health. Cancer-related fatigue (CRF), one of the most common treatment-related late effects, is known to seriously hamper survivors’ daily life activities such as attending school or work [8]. Another category of common late effects involves cardiovascular diseases caused by anthracyclines and/or radiotherapy over the chest [9–13]. Moreover, survivors treated with cranial irradiation are at an increased risk of developing endocrine disorders related to obesity [14]. Furthermore, it is now well established from a variety of studies that also health-related quality of life (HRQOL) of survivors can be severely compromised by the development of these and other late effects resulting from their past treatment [15–18]. The manifestation of these health conditions in cancer survivors can be negatively influenced by the presence of unfavourable lifestyle risk factors such as overweight, smoking behaviours and/or a low physical activity level. These concerns stress the need to adopt or to continue a healthy lifestyle for this population. This is supported by Jones et al., who found that in adult survivors of childhood-onset Hodgkin lymphoma, exercise can lower their risk of cardiovascular events in a dose-dependent manner [19].

